**Figure 1 F1:**
[figure not shown]
Study flow chart.

### Sample size

Main efficacy variable is the sum score of the BAI (values range from 0 to 63). A former study with a German sample of primary care patients observed a standard deviation of 11 and an intra-cluster correlation of 0.07 [76]. Therefore, a standardised effect size of 0.35 (that is 3.85 points on the original scale BAI) would be observed at a significance level of 0.05 by following up 130 patients. However, cluster randomisation is the method of choice for the present study. We expect a cluster size of six patients per practice. In consideration of the resulting design effect of 1.35, and the expected patient dropout-rate of approximately 20%, N = 444 patients from 74 general practices (37 practices per study arm) must be followed-up in order to detect a standardised effect size of 0.35 at a significance level of 0.05.

### Assignment of interventions

Cluster randomisation of general practices is stratified by population density of the administrative district in which the practice is located (that is ‘urban type of general practice’: urban versus rural). Computer-assisted randomisation is prepared by the trial statistician. An uninvolved person, who is not familiar to one of the GPs and not a member of the project team, generates the final randomisation list. The list is provided to the data management via an online randomisation tool.

The assignment of a certain general practice to one of the two study arms is performed by the data management as soon as the general practice is signalling the enrolment of patient(s) via fax. The data management retrieves allocation information for the general practice from the randomisation tool and sends it out to the general practice via fax and phone.

### Data collection and management

General practices collect clinical outcome data by handing out paper-moulded case report forms (CRFs) to patients on schedule (Figure 1). CRFs include patient self-reports on demographic data and outcome parameters (Table 1). As far as possible, CRFs are also handed out to patients who discontinue or deviate from intervention protocols. To ensure quality of assessments, practice teams are extensively trained in data collection procedures, and onsite monitorings are conducted by the project team.

The data management periodically recalls CRFs from general practices. CRFs are visually inspected for missing or ambiguous self-report items. A pre-defined list of self-explaining corrections is applied to CRFs. In cases where self-explaining corrections are not applicable, data queries are conducted by contacting GPs or patients. The paper-moulded CRFs are electronically scanned and then converted to TIF-files using ReadSofts’® FORMS software (Helsingbord, Sweden). Subsequently, the TIF-files are transferred to data sheets using IBM© SPSS® software (IBM Corp., Armonk, NY, USA). Data plausibility checks are performed by the data management. Data are retained for ten years after termination of the trial.

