## Methods/design

### Trial design

The study is a cluster randomised, non-blinded superiority trial with two parallel groups. General practices are treated as clusters. Allocation of clusters to two study arms (intervention versus control) is performed with a 1:1 ratio.

Cluster randomisation has been chosen to reduce the chance of contamination of interventions. Blinding is not possible, due to the character of the intervention. However, all patients should be kept blind to the allocation status, until completion of T0 baseline assessment, in order to minimise allocation bias.

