### Outcomes

The primary outcome parameter is clinical severity of anxiety, as measured by the widely used Beck Anxiety Inventory (BAI) [58,59]. The German version is well-validated. Good to excellent psychometric properties as well as sensitivity to treatment-related changes have been shown in primary care populations [60,61].

Secondary outcome parameters include: agoraphobic avoidance behaviour as measured by the ‘Mobility Inventory’ (MI; subscale ‘alone’) [62,63], number and severity of panic attacks as measured by the ‘Panic and Agoraphobia Scale’ (PAS; Items A1 and A2) [64,65], depressiveness as measured by the ‘Patient Health Questionnaire’ (PHQ-9) [66], patients’ perspectives on receipt of care as measured by the short form of the ‘Patient Assessment of Chronic Illness Care’ questionnaire (PACIC) [67,68], health-related quality of life as measured by the ‘EuroQol’ questionnaire (EQ-5D) [69,70], health service use and productivity losses as measured by a modified version of the ‘Client Sociodemographic and Service Receipt Inventory’ (CSSRI) [71,72], and quality adjusted life years (QALYs) as calculated from the EQ-5D [73].

Primary and secondary outcomes are based on self-report questionnaires that were chosen in consideration of established validity and good psychometric properties in primary care populations. Additional measures are used to address characteristics of the study population, potential confounders of efficacy parameters, or other methodological questions. Table 1 displays the outcome parameters and several of the additional measures. Additional interview studies are planned to highlight the feasibility and acceptability of the intervention from the viewpoint of GPs, HCAs, and patients.

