### Recruitment and timeline

General practices are recruited via invitation letters. In a first step, all general practices that are registered by the ‘*Kassenärztliche Vereinigung*’ in Thuringia (Germany) are invited to participate in the study (N = 1,251). If the response rate turns out to be too low to meet the required sample size, general practices from other parts of Germany will be invited by means of public relations. Eligibility criteria for general practices are checked via a questionnaire that has to be filled out by the GP and the HCA. To be enroled, the practice team has to give written consent to follow the study procedures.

Patients are recruited by the participating general practices. The recruitment procedure includes the following steps: (1) Patients of the general practice fill out a screening questionnaire based on the OASIS [74] and the PHQ panic module [11]. (2) Positively screened patients undergo a diagnostic interview conducted by the GP, who thereby uses a diagnostic manual that is based on validated ICD-10 checklists for PD and agoraphobia [75]. (3) If diagnosis of PD (ICD-10: F41.0) or PD/AG (ICD-10: F40.01) is confirmed during the diagnostic interview, other eligibility criteria for individual participants will be checked by the GP. (4) Eligible patients are verbally informed about the study by the GP who also hands out a written information sheet to them.^a^ (5) Eligible patients have to sign an informed consent form to be enroled.

Each general practice is instructed that six patients should be enroled to meet the aspired cluster size. In order to minimise selection bias, it is intended not to randomise a general practice before at least four patients have already been enroled in this practice. Recruitment of these four patients is expected within a time period of eight to twelve weeks. However, if a general practice fails to enrol at least four patients within this time frame, randomisation will be performed anyway.

Baseline (T0) and follow-up (T1, T2) assessments are administered via self-report questionnaires handed out to patients by the practice teams. Subsequent to T0, the interventions pertaining to individual participants start. Duration of the practice team-supported, self-managed exposure programme is about 23 weeks. Follow-up assessments are six (±one) months after baseline (T1) and twelve (±one) months after baseline (T2). Figure 1 displays the study flowchart.

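### The query rule does not keep GPs from supplying patients' BAI answers, and outcome forms pass through the unblinded treating practice

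*Protocol article*

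**What the plan says.** **Blinding.** Under Trial design: "The study is a cluster randomised, non-blinded superiority trial with two parallel groups". The reason follows: "Blinding is not possible, due to the character of the intervention". The one safeguard is that "all patients should be kept blind to the allocation status, until completion of T0 baseline assessment". No counterpart is given for T1 or T2.

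**Outcome.** Under Outcomes: "Primary and secondary outcomes are based on self-report questionnaires". The Statistical analyses section makes the BAI total at T1 the only confirmatory test.

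**Route of the forms.** Under Recruitment and timeline, T0, T1 and T2 "assessments are administered via self-report questionnaires handed out to patients by the practice teams". Data collection and management says the same ("General practices collect clinical outcome data by handing out paper-moulded case report forms (CRFs) to patients on schedule") and adds that data management periodically recalls the forms from the practices.

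**Queries.** In the same section, "CRFs are visually inspected for missing or ambiguous self-report items". A pre-defined list of self-explaining corrections is applied first. Where it does not help, "data queries are conducted by contacting GPs or patients". Nothing limits the GP route to GP-reported fields.

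**Safeguards described.** These are the correction list, training of practice teams in data collection, and onsite monitoring.

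**The concern.** The GP is not the source of a BAI answer. In the intervention arm the GP holds four appointments, and the health care assistant makes ten telephone contacts whose symptom and adherence results are reported to the GP. No such monitoring is described for control patients. An intervention GP asked about a blank BAI item would therefore have symptom information, and an interest in a programme that he or she delivered, which a control GP lacks.

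The programme lasts about 23 weeks and T1 falls at six months (±one month). The patient thus receives the T1 form from the coaching team at about the end of the coaching, and it goes back through the same practice.

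If either route moved scores differently by arm, the shift would enter the treatment contrast directly. The mixed model adjusts for baseline value and urban type, with practice as random factor; none of these terms can remove a measurement difference that runs along with the arm.

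**Working it through.** **1. The passages side by side**

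- *Can the query sentence be read as covering only GP-reported data?* Hardly. The inspection it follows from concerns self-report items, and the section describes the forms as patient self-reports on demographic data and outcomes.
- *Does it say that the GP answers for the patient?* No. It says whom to contact. Relaying and answering are both compatible with it.
- *Do the safeguards close the gap?* The correction list limits discretion for self-explaining cases only. Training and monitoring improve completeness and consistency. None of them separates the completed form, or the answer to a query, from the treating team.

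**2. The plan's own sample size**

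Inputs from the Sample size section: SD 11, difference 3.85 (0.35 SD), ICC 0.07, six patients per practice, 20% dropout, significance level 0.05. Assumed: two-sided test, 80% power, and the 130 patients read as per arm.

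- Patients per arm without clustering: 129 by calculation, against 130 stated.
- Design effect: 1 + (6 − 1) × 0.07 = 1.35.
- 130 × 1.35 = 175.5; 175.5 / 0.80 = 219.4, so 220 per arm. In whole practices: 37 × 6 = 222 per arm, 444 in total. The plan's figure reproduces.

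**3. Standard error of the treatment difference**

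- Analysed per arm: 222 × 0.80 = 177.6.
- Effective number per arm: 177.6 / 1.35 = 131.6.
- SE = 11 × √(2 / 131.6) = 1.36 points.

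**4. What an assumed differential shift would do**

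With no true effect and a shift of b points between arms, the two-sided type I error is Φ(b/SE − 1.96) + Φ(−b/SE − 1.96). The values of b are assumptions; the document gives none.

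| Assumed shift b (points) | Share of 3.85 | Type I error |
|---|---|---|
| 0 | 0% | 5% |
| 0.5 | 13% | 6.6% |
| 1.0 | 26% | 11% |

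**5. The query route alone**

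Suppose that a fraction of intervention patients have some items changed by one point each, all in the same direction.

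- 10% of patients, 2 items: 0.10 × 2 = 0.2 points, type I error about 5.3%.
- 20% of patients, 3 items: 0.20 × 3 = 0.6 points, type I error about 7.3%.

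These fractions are also assumptions. They suggest that the query route matters little by itself, and that a shift near one point would have to come mostly from how patients report on forms that pass through the practice.

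**The case against.** The trial openly declares itself non-blinded. After T0 patients know their treatment, and expectation effects in self-report would persist with any return route, so the change removes only an unknown part of the bias. Both arms use the same hand-out, return and query procedure, so only a differential part could distort the comparison. Hand-out by the practice has a merit: it also reaches patients who stop or deviate from the intervention, and with 20% dropout the power is only about 81%. All of this stands, and it argues for keeping the hand-out as it is.

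Several stronger readings are tempting, but the document does not support them:

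- *GPs fill in patients' BAI items.* The text says only that they may be contacted. The trial also holds GP-reported data (diagnosis, comorbidity, referrals), for which the GP is the right contact.
- *Patients rate their symptoms under the eyes of their coaches.* Nothing says that staff read the forms or are present at completion. Whether envelopes are sealed is a detail that an article may leave to the full protocol.
- *Data management knows the arm when it corrects forms.* That function retrieves the practice's allocation (Assignment of interventions), but clinical data carry research numbers (Confidentiality of data). Whether the same staff do both, or see the arm while correcting, is not stated.
- *The bias runs in one direction.* That it would favour the programme is a reasonable expectation, not something the document shows.

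What remains is a stated query rule that is too wide for a patient-reported primary endpoint, combined with a form route that runs through the treating team.

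**Conclusion.** The point holds as a weakness in a stated procedure, not as evidence of bias. The query rule permits a GP who delivers the intervention to resolve items of the self-reported confirmatory endpoint, and no described step separates the completed form from the practice team. This part of the measurement risk is avoidable even though treatment cannot be blinded.

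Its size is unknown. The range of about 6.6% to 11% rests on an assumed shift of 0.5 to 1 point, on the plan's SD, design effect and dropout, and on a two-sided 5% test. It ignores any gain in precision from baseline adjustment; a smaller standard error would make the same shift weigh more. The figures show sensitivity and are not an estimate of what will happen. The change is worth making because it is cheap and recruitment is still under way.

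**What to change.** - **Queries.** Amend Data collection and management so that only the patient answers queries on patient-reported outcome items. The GP may at most relay such a query, and answers only for GP-reported fields. Items that remain unanswered stay missing and are handled by a BAI scoring rule fixed in advance.
- **Return of forms.** Keep the hand-out by the practice to protect the return rate, but have patients seal the completed T1 and T2 forms in an envelope addressed to data management before the forms leave their hands.
- **Corrections.** Apply corrections and issue queries by research number without arm information, where existing staffing allows.

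Cost: up to 444 × 2 = 888 envelopes, some extra patient contacts and possibly a few more missing BAI items. Design, sample size and analysis model stay as they are.

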### Statistical analyses

All analyses are based on the intention-to-treat principle, including all enroled participants of randomised general practices providing data under treatment. If necessary, influence of missing data is analysed by means of additional sensitivity analyses.

All population characteristics and outcome efficacy data are presented with adequate descriptive statistics. The primary outcome (total score of BAI at follow-up T1) is analysed by means of a mixed linear model with general practice as random factor and treatment group, baseline value, and urban type of general practice as fixed factors. According to previous research, a normal distribution can be assumed for the present population [60]. The statistical test is performed at a significance level of 0.05 and is regarded as confirmatory. Estimators including 95%-confidence intervals are presented. Secondary outcomes are analysed by mixed linear models or generalised linear models, as appropriate. The tests for secondary outcomes are regarded as exploratory and performed at an uncorrected significance level of 0.05.

During the evaluation of population characteristics, special attention is paid to the success of randomisation. In case of major deviations, additional sensitivity analyses with potential confounding variables are performed (for example, age, sex, type of anxiety disorder under treatment).

With respect to the health-economic evaluation, direct and indirect costs of the treatments in both study arms are calculated. Administrative and market prices are used to valuate health service use. Productivity losses are valuated according to the human capital approach. In terms of an effect measure, quality adjusted life years (QALYs) are calculated from the EQ-5D [73]. A cost-effectiveness analysis is performed from a societal perspective, by calculating incremental costs per QALY. Non-parametric bootstrapping is used to estimate the uncertainty of the incremental cost-effectiveness ratio (ICER). Additionally, a net-monetary benefit regression analysis is performed.

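### The model class offered for some secondary outcomes, generalised linear models, makes no stated allowance for practice clustering; taken literally, its tests and intervals would be anti-conservative

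*Protocol article*

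**What the plan says.** Trial design in the protocol article sets the unit of randomisation: "General practices are treated as clusters", and "Allocation of clusters to two study arms (intervention versus control) is performed with a 1:1 ratio". Sample size carries this into the planning. An earlier German primary care sample "observed a standard deviation of 11 and an intra-cluster correlation of 0.07", and the number of patients is raised accordingly ("In consideration of the resulting design effect of 1.35").

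Statistical analyses then gives the primary endpoint, the BAI at six months, a linear mixed model. Practice is random; treatment, the baseline score and the urban/rural stratum are fixed. For everything else that section says "Secondary outcomes are analysed by mixed linear models or generalised linear models, as appropriate". It adds that the secondary tests are exploratory, at 0.05 without correction for multiplicity. It does not say which secondary outcome gets which class of model.

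**The concern.** The sentence attaches the word mixed to the first class of model and not to the second. Under the usual definitions the second class has no random effect and assumes independent observations; the class that adds a random effect is the generalised linear mixed model. Nothing else in the article supplies a practice effect, GEE or a cluster-robust variance for that branch. An analyst working from the text alone could fit patient-level models in a trial that allocated practices.

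Treatment is constant within a practice, so any positive correlation between patients of the same practice makes the naive standard error of the treatment effect too small. Such correlation is plausible here: the practice team delivers the programme, and in both arms the GP decides on referrals and other treatment. At stake are the p-values and 95% intervals of whichever secondary outcomes are analysed in this way.

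**Working it through.** **Inputs from Sample size.** BAI standard deviation 11, ICC 0.07, cluster size m = 6, dropout about 20%, target difference "a standardised effect size of 0.35 (that is 3.85 points on the original scale BAI".

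**The plan's own figures first.**
- Power and sidedness are not stated. Assuming 80% power and a two-sided 5% test, the normal approximation gives 2 × (1.960 + 0.842)² / 0.35² ≈ 128.1, so 129 per arm. The t-test gives 129.1, so 130. The stated 130 is therefore reproduced as a per-arm figure.
- Design effect: DE = 1 + (m − 1) × ICC = 1 + 5 × 0.07 = 1.35, as stated.
- 130 × 1.35 = 175.5; 175.5 / 0.8 = 219.4, so 220 per arm; 220 / 6 = 36.7, so 37 practices; 37 × 6 = 222 per arm and 444 in total, as stated.

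The clustering allowance in the planning is thus explicit and internally correct for the BAI.

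**What follows if an analysis makes no allowance for practice.** With equal cluster sizes, the correct standard error is √DE times the naive one. Hence:
- actual two-sided type I error = 2 × [1 − Φ(1.96 / √DE)];
- actual coverage of a nominal 95% interval = 1 minus that value.

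With 20% dropout, m = 6 × 0.8 = 4.8 patients followed per practice. At the BAI's ICC of 0.07:
- m = 4.8: DE = 1 + 3.8 × 0.07 = 1.266; √DE = 1.125; 1.96 / 1.125 = 1.742; type I error 8.2%, coverage 91.9%. Naive standard errors are 1 − 1/1.125 = 11% too small.
- m = 6: DE = 1.35; √DE = 1.162; 1.96 / 1.162 = 1.687; type I error 9.2%, coverage 90.8%. Naive standard errors are 1 − 1/1.162 = 14% too small.

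**Range.** The article gives no ICC for any secondary outcome, so the values below other than 0.07 are assumptions (m = 4.8):

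| ICC | DE | √DE | Type I error | Coverage |
|---|---|---|---|---|
| 0.02 | 1.076 | 1.037 | 5.9% | 94.1% |
| 0.05 | 1.190 | 1.091 | 7.2% | 92.8% |
| 0.07 | 1.266 | 1.125 | 8.2% | 91.9% |
| 0.10 | 1.380 | 1.175 | 9.5% | 90.5% |

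**The case against.** The strongest reply is that the article never says practice is left out. Generalised linear model describes an outcome distribution and a link; it can be loose shorthand for the mixed version, and such a model can also be fitted by GEE or with cluster-robust errors. The text excludes none of these. The context favours shorthand: the article calls practices clusters, inflates the sample size for them, and names practice as a random factor shortly before. The sentence does not repeat the practice term for the mixed linear models either. A condensed article may also leave such detail to an analysis plan that is not shown.

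Much of this stands, and it rules out several stronger readings that a reader might be tempted to draw:
- That the trial will ignore clustering in these analyses. That would be an inference from silence.
- That panic-attack counts, health service use or ordinal items are assigned to the unclustered branch. The article makes no such assignment and does not call any secondary outcome non-normal.
- That the true type I error is 8.2%. This needs two premises that the article does not supply: clustering is ignored, and the outcome shares the BAI's ICC.
- That the baseline value and the stratum are dropped from the secondary models. They are simply not repeated, which is detail that an article commonly leaves out.
- That the uncorrected 0.05 level aggravates the problem. It is openly declared for tests labelled exploratory.

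What does not stand is the suggestion that nothing needs changing. The article chose to name a model class, and the class named does not by itself fit a practice-randomised design. Exploratory status explains the absence of a multiplicity correction; it does not excuse intervals that cover less than they claim.

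**Conclusion.** The point holds as a wording defect with a conditional consequence. The article permits, for unspecified secondary outcomes, a class of model that taken literally treats patients of one practice as independent, and it states no remedy.

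If it were followed literally, tests and intervals would be anti-conservative. Type I error would be about 8% to 9% and coverage about 91% to 92% at an ICC of 0.07 with 4.8 to 6 patients per practice. Type I error would be about 6% to 9.5% over an assumed ICC of 0.02 to 0.10 at 4.8 patients per practice. These figures assume equal cluster sizes, and the 0.07 is the BAI's value borrowed for illustration.

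The confirmatory BAI analysis and the sample size are unaffected. The correction is worth making because it is cheap and removes a real ambiguity, not because the article shows that an invalid analysis is intended.

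**What to change.** Replace the sentence on secondary outcomes in Statistical analyses with: *Secondary outcomes are analysed by linear mixed models or generalised linear mixed models with general practice as random factor (or by GEE clustered by practice with a small-sample correction), as appropriate.* If an analysis plan already says this, aligning the protocol wording with it is enough.

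The cost is one sentence, with no further patients or data. Trial status reports recruitment as ongoing, so the change could be made before analysis. The downside is slightly wider intervals where clustering exists, which is the width they should have.
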